## Abstract

**Background:**

Treatment of chronic total occlusion (CTO) by percutaneous coronary intervention (PCI) is associated with the difficulty of guidewire manipulation through the occluded segment, particularly when there is hard tissue due to calcification. The purpose of this randomised controlled trial is to determine whether improved planning of CTO-PCI using coronary computed tomographic angiography (CCTA) (versus conventional angiography) increases success rates of wire crossing in ≤ 60 min in difficult cases.

**Methods:**

This is a randomised controlled open-label multi-centre trial in a superiority framework with 1:1 allocation ratio. Participants (*n* = 130) will be randomised into two groups: the study group who will receive standard of care with the addition of preoperative coronary computed tomographic angiography (CT group), and the control group that will receive standard of care (angiography group). The primary endpoint will be the rate of successful wire crossing in ≤ 60 min in complex CTO (J-CTO ≥ 2). Wire crossing will be considered successful if TIMI flow 3 is restored and residual stenosis is < 30%. The safety endpoint will be mortality due to the intervention or major adverse cardiac events (MACE). Secondary endpoints are success rates at any time; total time of PCI; time of wire crossing; rate of PCI complications; radiation levels during PCI; volume of iodine contrast medium administered; and cost of the PCI.

**Discussion:**

This randomised trial will provide insight into whether pre-procedural CCTA as opposed to conventional angiography for planning of CTO-PCI yield higher success rates of wire crossing in ≤ 60 min. Potential benefits of CCTA include shorter successful procedure times of CTO-PCI leading to less irradiation and contrast medium with lower complication rates.

**Trial registration:**

Clinical Trials.gov NCT04549896. Registered on December 21, 2021.

## Administrative information

Note: the numbers in curly brackets in this protocol refer to SPIRIT checklist item numbers. The order of the items has been modified to group similar items (see http://www.equator-network.org/reporting-guidelines/spirit-2013-statement-defining-standard-protocol-items-for-clinical-trials/).

## Introduction

### Background and rationale {6a}

Chronic total occlusion (CTO) refers to the complete obstruction of a coronary artery classified as Thrombolysis in Myocardial Infarction (TIMI) 0 flow for at least 3 months and is frequently diagnosed in patients with coronary artery disease [1–3]. Treatment of CTO can be categorised as non-invasive medical (aspirin, anti-cholesterol drugs, β-blockers, ACE inhibitors, nitrates, etc.), minimally invasive interventional (percutaneous coronary intervention (PCI)), or invasive surgical (bypass surgery). Since medical approaches often do not reduce symptoms or improve quality of life, minimally invasive interventions should be considered, especially in cases with angor/dyspnea, ischemia or ejection fraction reduction associated with viability of the myocardial wall, originally perfused by the occluded segment. The main challenge of CTO-PCI is the difficulty of guidewire manipulation in the correct trajectory through the occluded segment, particularly when there is hard tissue due to calcification. Technical developments and advances in algorithmic approaches to CTO-PCI resulted in higher success rates, reduced complications and improved procedural efficiency [3–5]; however, procedural success rates of CTO-PCI across studies range from 61 to 99% and are associated with procedural and anatomical difficulties [2]. The cardiologist has the choice of different PCI strategies (anterograde, retrograde, true to true, dissection re-entry) using most of the time a double vascular access (double radial, radial-femoral or double femoral). Due to the limited information about the occlusion anatomy, the antegrade wire escalation technique is often the first step to test the occlusion with softer wires before going up with stiffness and weight.

Different clinical models for lesion assessment have been proposed to assist cardiologists in choosing the ideal approach [2], of which the 5-point Japanese Multicentre CTO Registry (J-CTO) score is the most common [6]. The J-CTO score predicts the complexity of CTO-PCI as easy (0), intermediate (1), difficult (2), or very difficult (≥3), by assessing four characteristic features of the occluded section by conventional angiography: proximal cap shape, presence of calcifications, degree of bending, length of occlusion, and whether CTO-PCI has been attempted before. Nonetheless, scores derived from conventional angiography may not be sufficient to predict CTO-PCI difficulty, duration and outcome [7]. Coronary computed tomographic angiography (CCTA) enables non-invasive visualisation of proximal cap position and characteristics, of exact vessel trajectory and calcium distribution. This kind of information is less precise using conventional angiography. CCTA therefore offers a better evaluation of complex CTO, which could improve planning and outcomes of CTO-PCI, shorter procedure times, less radiation and less iodine contrast injection, as well as reduced costs and perhaps a higher success rate.

The purpose of this randomised controlled trial is to determine whether improved planning of CTO-PCI using CCTA (versus conventional angiography) increases success rates of wire crossing in ≤60 min in difficult cases (J-CTO ≥2). The primary endpoint will be the proportion of successful procedures, defined by TIMI flow 3 and stenosis < 30%, with wire crossing completed in ≤60 min. Secondary endpoints will include the proportions of successful procedures completed regardless the timeframe, time of wire crossing, radiation levels and volume of iodine contrast injected, and procedural complications. Safety endpoints will be mortality due to the procedure or any major adverse cardiac events (MACE).

### Objectives {7}

To determine whether improved planning of CTO-PCI using CCTA (versus conventional angiography) increases success rates (TIMI flow 3 and stenosis < 30%) of wire crossing in ≤60 min in difficult cases (J-CTO ≥2). To compare the proportions of successful procedures completed regardless the timeframe, time of wire crossing, radiation levels and volume of iodine contrast injected, procedural complications, and any major adverse cardiac events (MACE).

### Trial design {8}

A randomised controlled open-label multi-centre trial in a superiority framework with 1:1 allocation ratio.

### Eligibility criteria {10}

The authors will enrol 130 patients undergoing difficult CTO-PCI.

The inclusion criteria will be:Men and women aged 18 to 90 years with body mass index (BMI) ≤ 40 kg/m^2^;Coronary artery chronic total occlusion (TIMI flow 0 for > 3 months) associated with myocardial viability (intended like normokinetic/hypokinetic wall motion or instrumental data in favour of viability) associated with ≥ 2 Canadian Cardiovascular Society (CCS) angina or ≥ 2 New York Heart Association (NYHA) dyspnoea or documented ischemia or ejection fraction < 50%;Coronary angiography J-CTO score ≥ 2;Understanding of, and agreement to comply with the study procedures;Signature of informed consent form prior to any study-related procedures; andAffiliation to social security scheme.

The exclusion criteria will be:Coronary angiography J-CTO score of 0 or 1;Pregnancy or other protection by law;Very frequent irregular cardiac rhythm (arrythmia?/tachycardia?) > 100 beats/min;Concomitant pathologies that introduce additional risks, such as hemodynamic instability, anaemia < 9 g/dl, gastrointestinal bleeding, thrombocytopenia with < 50,000/mm^3^ platelets count or severe valvular disease; orCT-scan performed before inclusion into the study.

### Who will take informed consent? {26a}

Participants in the study will sign the written informed consent which will be collected by the cardiologist (principal investigator) who will perform the CTO-PCI.

### Additional consent provisions for collection and use of participant data and biological specimens {26b}

Not applicable.

## Interventions

### Explanation for the choice of comparators {6b}

Participants will be randomised into two groups with a 1:1 allocation: the study group who will receive standard of care with the addition of preoperative CCTA-scan (CT group), and the control group that will receive standard of care (angiography group).

### Intervention description {11a}

#### Preoperative assessment

The following assessments will be performed as part of the standard of care for the diagnosis of CTO:Conventional coronary angiographyIf symptoms and viability are not established through angiography, the patient will undergo one of the following:aStress electrocardiogram (ECG)bCardiac magnetic resonance imaging (MRI)cStress echocardiographydMyocardial scintigraphyCollection of biological markers: troponin, creatine kinase, creatinine, clearance of creatinine, haemoglobin. Preoperative angiography will be performed for all patients in ambulatory settings under local anaesthesia, with either a radial artery or femoral artery approach, with the former being the first choice if the artery is of good quality. An introducer sheath measuring 4 or 5 French (Fr.) is advanced within the artery using the Seldinger technique, and a catheter is advanced through the introducer up to the heart. A 6–8 cc iodine contrast injection in the coronary artery ostia allows visualisation of coronary artery anatomy under radiography. A picture registration is obtained and archived for planning of CTO-PCI. During the procedure heparin and nitrates are administrated.

If conventional angiography indicates a J-CTO score ≥2, the patient will be enrolled in the study, if they meet the eligibility criteria. Patients will then be randomly allocated to the CT group or angiography group. Patients in the CT group will undergo an additional CCTA scan (GE CT Revolution Scan 256; Iomeron 350 iodine contrast). The total dose length product (DLP, mGy/cm^2^) and computed tomography dose index (CTDI, mGy) will be recorded. Iodine contrast for the CCTA will be 55ml (10ml saline–55ml Iomeron 350–20ml saline at 5ml/s).

For the CT group, the PCI strategy will be based on:J-CTO scores derived from conventional angiography as well as CCTA, to assess five characteristic features of the occluded section: proximal cap shape, presence of calcifications, degree of bending, and length of occlusion, as well as whether CTO-PCI has been attempted before.CT RECTOR (Computed Tomography Registry of Chronic Total Occlusion Revascularization) score, to assess: the presence of multiple occlusions, the stump morphology, degree of calcification and bending, as well as whether previous CTO-PCI has been attempted before.Calcium score of the occluded artery and occluded segment to assess the calcium distribution (full moon, eccentric > 50% or < 50%, circumferential) at the proximal and distal cap as well as the body of the occlusion; andInspection of the occluded coronary artery anatomy as visualised on the CCTA.

For the angiography group, the PCI strategy will be based on the J-CTO score derived from conventional angiography. The occlusion is assessed based on its proximal cap shape, presence of calcifications, degree of bending, and length. The patient history is assessed to determine if CTO-PCI has been attempted before.

### CTO-PCI

The recanalisation procedure is the most complex type of percutaneous coronary angioplasty. A double radial access or a radial/femoral access is used in most of the patients. A simple arterial access is used in the case of ipsilateral collateral circulation. The first and most complex step is to go through the occluded segment with a 0.08- to 0.014-inch tip guidewire to access the true lumen in the distal part of the artery, by one or more of the following approaches: anterograde, retrograde, dissection/re-entry (anterograde or retrograde). A double arterial access is often necessary to visualise the distal part of the artery through the collateral circulation and to go retrograde if necessary.

### Criteria for discontinuing or modifying allocated interventions {11b}

Treatment for some individuals that fulfilled the eligibility criteria and were allocated into the study or control group may be discontinued or modified if they present with:New disease that requires an urgent intervention which doesn’t permit antiplatelet treatment due to bleeding risk,COVID-19 infection,Septic status, orA disease that affects the patient’s autonomy.

### Strategies to improve adherence to interventions {11c}

Not applicable, as the nature of the intervention is a one-off delivery of CTO PCI, rather than a series of steps that require adherence.

### Relevant concomitant care permitted or prohibited during the trial {11d}

As per standard of care, mandatory dual antiplatelet therapy has to be taken in both the CT group and angiography group due to PCI, which is composed of one of three options:Option 1: Aspirin 150 mg/day and clopidogrel 150 mg/day for the first month; aspirin 150 mg/day and clopidogrel 75 mg/day for the 5 months following; and only aspirin 160 mg/day without interruption after 6 months. Load of clopidogrel: 600 mg once, more than 12 h before the PCI.Option 2: Aspirin 75 mg/day and ticagrelor 90 mg 2 times/day for the first 6 months; aspirin 160 mg/day alone without interruption after 6 months. Load of ticagrelor: 180 mg once, more than 6 h before the PCIOption 3: Aspirin 75 mg/ day and prasugrel 10 mg/day for the first 6 months; aspirin 160 mg/day without interruption after 6 months. Load of prasugrel: 60 mg once, more than 6 h before the PCI

Single antiplatelet therapy will be administered in case of concomitant anticoagulant treatment, comprising clopidogrel 150mg/day for 1 month and then 75mg/day for 6 months, aspirin 75mg/day or clopidogrel 75mg day after 6 months. Load of clopidogrel: 600mg more than 12 h before the PCI.

In case of chronic renal insufficiency (clearance of creatinine <47ml/min), hydration with 1000 ml saline will be necessary before the CT scan and before the CTO-PCI. In case of allergy to contrast medium, antihistamines and corticosteroids will be taken before the CT scan and before the CTO-PCI.

The immediate result of the CTO-PCI procedure will be evaluated during the first two days of hospitalisation after the procedure. As part of standard of care, treatments and activities will be monitored:Metformin will be suspended 24 h before and 48 h after CTO-PCI.Anticoagulants will be suspended 72 h before CTO-PCI.Blood samples will be collected before and one day after CTO-PCI to evaluate coagulation, renal function, troponin, creatine kinase, platelet count and haematocrit.

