### Outcomes {12}

The primary objective of this study is to compare rates of successful wire crossing in ≤60 min in complex CTO (J-CTO ≥2) among the CT group and angiography group. Wire crossing will be considered successful if TIMI flow 3 is restored and residual stenosis is <30%. TIMI flow and residual stenosis will be evaluated by a pool of two cardiologists who are not directly involved in the procedure, and who are blinded to group allocation. The TIMI flow scale is classified as Grade 0 to 3 (Table 1).

**Table 1 Tab1:** TIMI flow grades

Grade 0	No flow
Grade 1	penetration without perfusion in the distal part of the artery
Grade 2	partial perfusion, the iodine contrast goes across the obstruction and fills the distal part of the artery, but the flow and the clearance of the iodine contrast are perceptibly slower if compared to the other non-occluded segments/arteries
Grade 3	complete perfusion, anterograde flow into the distal part of the artery with rapid filling and clearance if compared to the other segments/arteries.

The secondary objectives of the study are to compare:Success rates at any timeTotal time of PCI (minutes)Time of wire crossingRate of PCI complications (Major Adverse Cardiac Events, MACE): death, coronary perforation with cardiac tamponade requiring pericardiocentesis, myocardial infarction (if elevation of troponin or creatine kinase associated with change in electrocardiogram), stroke, major bleeding with loss of haemoglobin > 3 g/dl.Radiation levels during PCI expressed as transferred kinetic energy (air Kerma, Gy), dose area product (DAP, mGycm^2^), and fluoroscopy time (minutes).Volume of iodine contrast medium administered during PCI (millilitres).Cost of the PCI (euros) CTTA (CT group) Angiography Preoperative assessment, as summarised in the material invoice of every procedure.

Renal adverse events will be assessed after diagnostic coronary angiography, CCTA (CT group only), and CTO-PCI. Clinically relevant findings (like contrast allergic reaction) will be reported as adverse events. Their relationship with the CT scan or CTO-PCI will be reported. Other symptoms, such as angina CCS class, dyspnea NYHA class, MACE and renal failure will be recorded. Biologic markers, such as troponin, creatine kinase, creatinine, clearance of creatinine, and haemoglobin, will be recorded after CTO-PCI.

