### Adverse event reporting and harms {22}

All adverse events have to be registered in the eCRF. An adverse event is considered as serious if there is death or life-threatening circumstances, inpatient or prolonged hospitalisation, persistent or significant incapacity or substantial disruption of the ability to conduct normal life functions, congenital anomaly or an event judged as serious by the Investigator.

The medical judgement of the investigator could manage to declare some other events considered as potentially serious (especially some biological anomalies). Expected serious adverse events and unexpected serious adverse events will have to be distinguished.

The investigator must, for each serious or non-serious adverse event, describe them on a form in the eCRF. The etiological diagnostic (rather than symptom), the date of the beginning, the seriousness, the intensity, the action taken with the experimental product or the study procedure, the corrective treatment administered and the causal link between treatment or procedure and serious adverse event have to be described. When the event is considered as serious, the investigator has to inform the trial steering committee immediately after having known of the events. Within 8 days after the declaration, the investigator may provide additional relevant information to the trial steering committee. If a patient declares a serious adverse event, he will be followed until the resolution of this adverse event, a stabilisation considered as tolerable or a return to the previous statement even if the patient is withdrawn from the study. Any serious adverse event associated to a study participant has to be declared from the date of consent form signature and during all the follow-up duration. If the serious adverse event is related to the study procedure, there is no time limitation of participant follow-up.

Risks related with the CT scan, object of our evaluation: as CT scan can be performed as part of standard of care for pathology diagnosis, there is no additional risk related to this investigation performed in the study. Risks will be the same risks as those related to the angiography necessary to visualise coronary arteries before and during the recanalisation procedure, as the contrast medium used is the same:IrradiationContrast-induced nephropathy in patients with renal insufficiencyAllergic reaction to radiographic contrast media

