What is the frequency?Allergic reactions to iodinated contrast media are very infrequent: 1.5 events per 1000, of which 2.6% is serious [10].Incidence of renal insufficiency requiring dialysis is < 1% and the development of the complication is correlated with a dose of contrast > 100 ml, clearance of creatinine < 47 ml/min, diabetes [9].

How those risks can be managed or reduced?Reduction of cardiac rate to obtain a good quality exam with low irradiation.Anti-allergic treatment before contrast injection for the atopic patients.

Hydration for patients with chronic renal insufficiency (creatinine clearance <47ml/min), metformin-free period for diabetic patients 24h before and 48h after the contrast injection compared to the volume of contrast medium used during standard angiography and PCI, the volume of contrast medium for the CT scan is low (55ml).

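### The care section {11d} ties the metformin rule to the PCI only and premedication to contrast allergy, while the risk section {22} ties them to the contrast injection and to atopy; the two must be reconciled

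*Protocol article*

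**What the plan says.** All references are to the Protocol article.

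**Metformin.** Relevant concomitant care {11d}: "Metformin will be suspended 24 h before and 48 h after CTO-PCI". Adverse event reporting and harms {22}: "metformin-free period for diabetic patients 24h before and 48h after the contrast injection". The second statement belongs to the answer on how risks can be managed, in a block that opens with "Risks related with the CT scan, object of our evaluation".

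**Anti-allergic premedication.** {11d}: "In case of allergy to contrast medium, antihistamines and corticosteroids will be taken before the CT scan and before the CTO-PCI". {22}: "Anti-allergic treatment before contrast injection for the atopic patients".

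**Hydration.** Both sections use a creatinine clearance below 47 ml/min. {11d} requires 1000 ml saline ahead of both the CT and the PCI.

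**Single antiplatelet therapy with a concomitant anticoagulant.** {11d}: "clopidogrel 150mg/day for 1 month and then 75mg/day for 6 months, aspirin 75mg/day or clopidogrel 75mg day after 6 months".

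**Exposure and outcomes.** The CCTA is given to the CT group only: "Iodine contrast for the CCTA will be 55ml" (Preoperative assessment). Outcomes {12} states: "Renal adverse events will be assessed after diagnostic coronary angiography, CCTA (CT group only), and CTO-PCI". It also has contrast allergic reactions reported as adverse events, with their relationship to the CT or the PCI.

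**The concern.** {11d} is where a site looks for care instructions. For hydration and premedication it names both contrast procedures, so leaving the CT out of the metformin sentence reads as a limit on that rule. {22} nevertheless lists a metformin-free period around contrast among the measures that manage the CT's risks. The protocol therefore relies, for an exposure that only one arm receives, on a measure that its care section does not apply to that exposure.

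For premedication, the two sections select patients by different criteria. A site following one section would treat a different group from a site following the other.

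The trial is multi-centre. If sites read these passages differently, handling around contrast would vary for reasons unrelated to the randomised comparison. That would blur the renal and allergic events that {12} intends to relate to the CT or to the PCI. It is also a patient-safety matter in its own right, because {22} names diabetes among the correlates of renal complications.

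**Working it through.** **1. Scope of the metformin rule.** The durations are identical: 24 h before, 48 h after. Only the anchor differs, being the PCI in {11d} and the contrast injection in {22}. Since {22} is discussing the study CT, its rule covers the CCTA.

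**2. Does the PCI window cover the CT anyway?** Set the PCI at hour 0. The {11d} window runs from −24 h to +48 h. Table 2 in Participant timeline {13} places the CT at D0 −1 to 30 days, read here as 1 to 30 days before PCI. A CT on day −d is at hour t = −24d, and the {22} interval around it runs from t − 24 to t + 48. The overlap of an interval [a, b] with the {11d} window is max(0, min(b, 48) − max(a, −24)).

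| CT day | 24 h before CT: hours covered | 48 h after CT: hours covered |
|---|---|---|
| −1 | [−48, −24]: 0 | [−24, 24]: 48 |
| −2 | [−72, −48]: 0 | [−48, 0]: 24 |
| −3 | [−96, −72]: 0 | [−72, −24]: 0 |
| −4 to −30 | 0 | 0 |

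No CT day has its full interval covered. On 28 of the 30 possible days (−3 to −30), none of it is covered.

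**3. Who is premedicated.**

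| Patient | {11d} | {22} |
|---|---|---|
| Known contrast allergy, not atopic | covered, drug classes named | not named |
| Atopic, no known contrast allergy | not named | covered, no drug class named |
| Both | covered | covered |

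{11d} applies premedication at the CT and at the PCI, and {22} applies it before contrast. The mismatch therefore bears on the CT in the CT arm and on the PCI in both arms.

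**4. Hydration.** The clearance threshold is the same in both places, so there is no conflict.

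**5. Single-antiplatelet steps.** In sequence, 1 + 6 = 7 months, while the next step begins after 6 months. Dual-therapy Option 1 in the same section gives 1 + 5 = 6 months and is consistent with its own switch. The overlap is month 7. Participation ends 6 months after PCI (Provisions for post-trial care {30}; close-out at D0 +180 days in Table 2). The later step allows either aspirin 75 mg or clopidogrel 75 mg, so a patient who stays on clopidogrel has the same drug and dose in month 7 on either reading.

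**6. Number of patients.** The documents give no figures for diabetes, metformin use, atopy, contrast allergy or anticoagulant use. The CT arm is planned at 65. If diabetes prevalence is assumed to be 20% to 40%, the arm has 0.20 × 65 = 13 to 0.40 × 65 = 26 diabetic patients. That counts diabetics, and the number taking metformin would be no larger.

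**The case against.** The strongest reply is that nothing here is a true contradiction. The metformin interval is the same in both sections, and {11d} does not say that metformin continues at the CT. Its sentence stands in a list whose items all concern the PCI admission. {22} supplies the rule for the CT, and the two sections belong to one protocol. Likewise, neither premedication sentence says it is the only trigger, so a site can apply both. This stands: the passages are compatible if read together. It does not remove the point, because {11d} names the CT for hydration and premedication and omits it for metformin, so a site using {11d} alone would reasonably take that rule to concern the PCI only.

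A second reply is that the numbers are small. {22} cites 1.5 allergic reactions per 1000. Taken per administration, 65 CT scans give 65 × 0.0015 ≈ 0.1 expected reactions. The same section puts renal insufficiency requiring dialysis below 1%. This also stands: no material effect on the trial's results is shown.

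A reader might infer three stronger things that the documents do not support:

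- **That the variation is confined to the CT arm.** This is so for metformin at the CCTA, but the premedication mismatch also reaches the PCI in both arms.
- **That patients with renal insufficiency face conflicting rules because of their renal function.** Hydration agrees, and neither metformin sentence depends on creatinine clearance.
- **That the antiplatelet overlap affects every anticoagulated patient in the trial.** It falls after participation ends and matters only for those moved to aspirin.

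**Conclusion.** The point holds as a wording inconsistency with safety relevance. {11d} as written sets no metformin rule at the study CT, where {22} relies on one, and the two sections name different groups for premedication. The timing result rests on reading Table 2 as 1 to 30 days before PCI. Any divergence in practice depends on a site using one section without the other.

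Its size in patients cannot be derived from the documents. The 13 to 26 diabetic patients rest on an assumed prevalence, and the conclusion does not depend on them. The primary endpoint, the sample size and the main comparison are untouched. The consequence is for patient safety and for interpreting renal and allergic adverse events. The single-antiplatelet sentence is a minor drafting fault with no bearing on outcomes collected within follow-up. No view is taken on which clinical rule is right.

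**What to change.** The sponsor and investigator should reconcile {11d} and {22}:

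- State once, in {11d}, whether the metformin rule applies at the CCTA as well as at the PCI.
- State once, in {11d}, which patients receive premedication and before which procedures.
- Replace the parallel statements in {22} with a cross-reference to {11d}.
- Reconcile the durations of the single-antiplatelet steps with the time of the switch.

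The clinical content is for them to decide. The cost is a wording correction and a note to sites, through the protocol's own amendment procedure if they judge the change substantial. It needs no extra patients, visits or analyses.
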